## Testing the hypothesis

All adult patients (> 18 years) starting intravenous and/or oral antibiotic treatments during hospitalisation will be included in the study. Written informed consent will be obtained by every patient before study inclusion. Exclusion criteria will be pregnancy and recent nose surgery. Patients starting antibiotic therapy *per os *and/or intravenously will be sampled at antibiotic start (t_0_, within one hour) and at the following intervals: day 3 (t_1_), 7 (t_2_), 15 (t_3_), 30 (t_4_) (Figure 1). Patients colonised with MRSA and/or extended-spectrum β-lactamase (ESBL)-producing gram-negative bacteria before starting antibiotic therapy (t_0 _sample) will be excluded from follow-up cultures and analysis. Patients will be followed during the hospitalisation and afterwards for a total of 30-day from the inclusion in the study. Screening will be performed in outpatient clinics after patients' discharge from the hospital, if possible.

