### Outcomes

The primary outcome will be the rate of acquisition of target antibiotic bacteria by 1,000 antibiotic-days in hospitalised patients. The rate will be also defined according to antibiotic class and single drug. Patients will be stratified by class of risk (e.g., cirrhosis, diabetes, malignancies) and rate of acquisition will be defined. The secondary outcome will be the rate of nosocomial infections by 1,000 days of hospitalisation in newly colonised patients after undergoing antibiotic therapy.

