### Statistical analysis

The assessable population for each target organism will include all treated patients from whom baseline screening and at least one follow-up screening will be available. The incidence of colonisation will be defined by the number of new cases of colonisation for 1,000 days of antibiotic therapy. Only patients with a negative baseline (t_0_) will be included in the longitudinal analysis. The length of exposure to antibiotic therapy for patients newly colonised by ARB will be defined by the number of days between the inclusion in the study and the date of the first positive sample. The length of exposure to antibiotic therapy for patients not colonised will be defined by the number of days between the inclusion in the study and the date of antibiotic discontinuation. The colonisation pressure will be calculated for each center and defined as the average point of prevalence for antibiotic-resistant bacteria for all days until acquisition or discharge. Time-to-event analysis (in days) between the inclusion in the study and the acquisition of colonisation will be done using Kaplan-Meier curves and Cox proportional hazard regression modeling in which the number of days until acquisition will be the dependent variable. Two nested case-control studies will be performed:

#### Case control study 1

To define the impact of antibiotics on new acquisition of MRSA and ESBL-producing *Enterobacteriaceae*, a matched case-control study will be done (ratio 1:4). The control group will be selected among patients not receiving antibiotics, admitted in the same ward on the day of the corresponding case, with negative cultures at hospital admission. Matching criteria will include: age (± 5 years), sex, and total length of hospitalisation.

#### Case control study 2

To define individual level of risk related to specific antibiotics, patients acquiring MRSA and ESBL-producing *Enterobacteriaceae *will be compared with patients not acquiring ARB after starting antibiotic therapy (ratio 1:4). Previously known risk factors or clinically relevant significant variables from the univariate analysis will be considered for inclusion in multivariate logistic regression analysis. The Hosmer and Lemeshow goodness-of-fit test will be used to assess model fit.

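### The primary rate mixes two exposure clocks: off-drug acquisitions can enter the numerator while non-acquirers' off-drug time is left out, so it is not per antibiotic-day and is inflated most for short courses

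*Protocol article*

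**What the plan says.** The Outcomes section states: "The primary outcome will be the rate of acquisition of target antibiotic bacteria by 1,000 antibiotic-days in hospitalised patients". It adds: "The rate will be also defined according to antibiotic class and single drug". The Implications section also promises this rate by duration of therapy.

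The Statistical analysis section fixes the numerator and denominator: "The incidence of colonisation will be defined by the number of new cases of colonisation for 1,000 days of antibiotic therapy". It then defines one term, the length of antibiotic exposure, in two ways. For newly colonised patients it is "the number of days between the inclusion in the study and the date of the first positive sample". For patients not colonised it is "the number of days between the inclusion in the study and the date of antibiotic discontinuation".

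Under Testing the hypothesis, swabs are scheduled at days 3, 7, 15 and 30 from antibiotic start, and "Patients will be followed during the hospitalisation and afterwards for a total of 30-day from the inclusion in the study". Neither the swabs nor the follow-up depends on the patient still being treated. After discharge, swabs are taken where possible.

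**The concern.** The numerator has no condition that the patient is still on the drug. A patient treated for 7 days who first tests positive on day 30 is a new case and contributes 30 days under an antibiotic-exposure label, of which 23 are off drug. A patient treated for 7 days who stays negative to day 30 contributes 7 days, although that patient was at risk and swabbed for the other 23.

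The off-drug period therefore supplies events, but the off-drug time of most patients is discarded. The result is neither an on-drug rate nor a 30-day rate. The shorter the course, the more time is discarded, so drugs usually given in short courses look worse than drugs given in long ones at the same daily risk. This affects the primary outcome, its breakdown by class and drug, and above all the breakdown by duration. The Implications section raises shorter treatment as a possible benefit, and this rule pushes the rate up for short courses, so it could mask or reverse such an effect.

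**Working it through.** **Inputs from the article.** Swab days 3, 7, 15 and 30; the two exposure definitions; 3% MRSA acquisition and 5% ESBL acquisition (Sample size). The article gives no rate per 1,000 days to reproduce. Its 3% does match its own enrolment figure: 8565 × 0.03 = 256.95, against 257 planned MRSA cases.

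**Assumptions (not in the article).** Course length *D*; constant on-drug hazard *h*; off-drug hazard *r* × *h*; all swabs taken unless stated.

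**Step 1: equal hazard on and off drug, rounded counts.** Take *h* = 0.001 per day, about 3% over 30 days. Per 1,000 patients the first positives at days 3, 7, 15 and 30 are 3, 4, 8 and 15, so 30 cases. They contribute 3×3 + 4×7 + 8×15 + 15×30 = 607 days. The 970 non-acquirers contribute *D* days each.

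- *D* = 3: 30 / (607 + 970×3) = 8.5 per 1,000
- *D* = 7: 30 / (607 + 970×7) = 4.1 per 1,000
- *D* = 14: 30 / (607 + 970×14) = 2.1 per 1,000
- *D* = 30: 30 / (607 + 970×30) = 1.0 per 1,000

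The true rate is 1.0 in every row. With non-acquirers followed to day 30, the rate is 30 / (607 + 970×30) = 1.0 whatever the course length.

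**Step 2: which clock causes the inflation.** If acquirers were also cut at drug stop, the 3-day course would give 30 / (30×3 + 970×3) = 10.0, against 8.5 under the written rule. The acquirers' off-drug days thus lower the rate. The inflation comes from off-drug events combined with the truncated time of non-acquirers.

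**Step 3: lower risk off drug.** Set *h* = −ln(0.97)/30 = 0.001015 (3% if treated for all 30 days) and *S*(*t*) = exp[−*h*·min(*t*, *D*) − *r*·*h*·max(*t* − *D*, 0)]. First positives at each swab are the drop in *S* since the previous swab; *P* is their sum. The written rate is *P* / [Σ(events × swab day) + (1 − *P*)·*D*], and inflation is that rate divided by *h*.

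Example, *D* = 7 and *r* = 1/4: first positives per 1,000 are 3.04, 4.04, 2.01 and 3.77, in all 12.86, contributing 180.6 days. The rate is 12.86 / (180.6 + 987.14×7) = 1.81 per 1,000, and 1.81 / 1.015 = 1.8.

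Inflation over the true on-drug rate:

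| Off-drug / on-drug hazard | 3-day course | 7-day | 14-day |
|---|---|---|---|
| 1 | 8.4× | 4.0× | 2.1× |
| 1/2 | 5.0× | 2.6× | 1.55× |
| 1/4 | 3.1× | 1.8× | 1.3× |
| 1/10 | 1.9× | 1.3× | 1.1× |
| 0 | 1.0× | 1.0× | 1.0× |

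At 5% over 30 days and equal hazard the written rates are 13.0, 6.5 and 3.5 per 1,000 for 3, 7 and 14 days, against a true 1.7.

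**Step 4: missing late swabs.** Use the Step 1 counts. If half the patients have no swab after day 7, the cases are 3 + 4 + 4 + 7.5 = 18.5, with 9 + 28 + 60 + 225 = 322 days.

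- *D* = 7: 18.5 / (322 + 981.5×7) = 2.6 per 1,000, instead of 4.1
- *D* = 3: 18.5 / (322 + 981.5×3) = 5.7
- *D* = 14: 18.5 / (322 + 981.5×14) = 1.3

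The level falls, but the 3-day to 14-day ratio stays at about four. If nobody on a 7-day course is swabbed after day 7, the rate is 7 / (37 + 993×7) = 1.0 and the inflation is gone.

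**The case against.** No sentence says outright that off-drug acquisitions count in the primary rate. The Outcomes section speaks of hospitalised patients, post-discharge swabs are taken only where possible, and the full protocol may say which swabs count. This has weight: the reading is an inference from an unrestricted numerator and a fixed swab schedule. But nothing in the article excludes such events, and the acquirers' clock runs to the first positive sample with no reference to drug stop. The two clocks are stated rules, not details left out.

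The sizes also depend on off-drug risk and swab completeness, which the article does not give, so the four-fold figure for a 7-day course is the upper end of the range tested. That stands. There is an opposing bias as well: a non-acquirer with a single follow-up swab is credited with days to drug stop, including unobserved days after that swab. Drug-specific risk is also examined in case-control study 2, so it does not rest on this rate alone; the primary outcome does.

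Three stronger readings are tempting and are not supported:

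- A reader might infer that Kaplan-Meier and Cox censor non-acquirers at drug stop. The article describes time from inclusion to acquisition and does not say that the exposure lengths serve as follow-up times.
- A reader might extend the argument to single-day courses, where the distortion would be greatest. The article does not say that such courses are enrolled.
- A reader might blame the acquirers' extra days for the inflation. They work the other way.

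**Conclusion.** The point holds in conditional form. As written, the primary rate is not a rate per antibiotic-day. It is inflated whenever some acquisitions occur and are sampled after drug stop, and at every positive off-drug hazard tested the inflation is larger for shorter courses. Under a 3% 30-day risk with complete swabs, the range is 1.0 to 8.4-fold for 3 days, 1.0 to 4.0-fold for 7 days and 1.0 to 2.1-fold for 14 days, as off-drug hazard goes from none to equal. Missing post-discharge swabs shrink it. The lower end requires no off-drug acquisition at all, or none sampled; yet the Background section names the period soon after therapy as part of the question. A larger sample does not help, because this is bias. Confidence is high in the inconsistency and its direction, and moderate in the size.

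**What to change.** Apply one rule to events and days for every patient. For the primary rate, count acquisitions and person-days from inclusion to the earliest of first positive swab, last swab, and end of therapy plus a pre-stated carry-over period. That period should be the same number of days for all patients and drugs. It should not be set as the next scheduled swab, because that gap varies with course length. Report later acquisitions separately per 1,000 off-drug person-days. State that Kaplan-Meier and Cox follow all patients to first positive or last swab, not to drug stop, with antibiotic exposure as a time-updated covariate.

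The cost is rewording and reprogramming. Duration of therapy (Variables section) and swab dates are already planned data. The headline rate will be lower than under the present rule if off-drug acquisitions occur. For some acquisitions, timing relative to drug stop will be known only to the interval between two swabs, so the plan should say how these are assigned and test that choice in a sensitivity analysis.

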The likelihood of acquisition of nosocomial ARB during or shortly after therapy with different antibiotic agents is still unclear and is often confounded by scarce data on antibiotic usage at the individual patient level. Study design, selection bias, definition of control groups and failure to control for confounding variables might account for conflicting results [8]. No prospective multi-centre cohort study has been conducted defining, in countries with varying baseline antimicrobial resistance rates, the impact of antibiotic exposure on the development and acquisition of nosocomial carriage by ARB, after accounting for individual and group-level confounding variables, such as case-mix and colonisation pressure [8-10].

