## Presentation of the hypothesis

We designed a 2-year observational cohort study (WorkPackage 4 of the EU-funded SATURN project) in order to clarify and determine the role of antibiotic therapy in the acquisition of ARB in hospitalized patients. The study will run in three European hospitals, ranging from 700 to 3,500-bed capacity: Università Cattolica Sacro Cuore "Policlinico A. Gemelli" (UCSC, Rome, Italy), Institute of Infectious Diseases "Matei Bals" (IDMB, Bucharest, Romania), and Clinical Center of Serbia (CCS, Belgrade, Serbia). Overall, 6 medical and 6 surgical wards will be included. All centers obtained ethical approval from the local institution review board.

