## Implications of the hypothesis

SATURN project is a European multicentre study that aims to provide an in-depth knowledge of ARB acquisition through the analysis of antibiotic classes, duration of treatment and dosage in the nosocomial setting by a multidisciplinary approach. The SATURN project website http://www.saturn-project.eu provides the information and details concerning the different WPs and the entire project.

Several outcomes will be obtained at the end of the study (December 2014, expected): the rate of acquisition of target ARB by 1,000 antibiotic-days according to different classes of antibiotics, duration of therapy, and antibiotic combinations (monotherapy versus combinations); risk factors associated with new colonisation by target ARB; and risks for nosocomial infections due to target ARB after a cycle of antibiotic therapy adjusted by length of hospitalisation and ward colonisation pressure.

The WP4 study is currently recruiting patients in all clinical centers. The accomplishment of the study will be pursued thanks to the great strive of all clinicians, nurses and microbiology staff in every study step. An advertising campaign (posters, stickers and pictures) was performed in the selected wards in order to thrill and sensitise the recruited staff.

The results of the study should lead to the design of specific infection control measures for preventing spread of ARB in hospitalised non-ICU patients undergoing antibiotic therapy. A potential benefit for selective screening in high-risk patients during antibiotic therapy or shorter duration of antibiotics in such patients might be hypothesised. Readily available colonisation information could impact empiric therapy for nosocomial infections or, for example, the potential need of mupirocin prophylaxis for patients colonised by MRSA during hospitalisation. Assessment of the usefulness of the recommendations derived from the results of the SATURN study should be of valuable help for those in charge of infection control, for hospital administrators, and for those managing budgets of large healthcare organisations.

We do expect that SATURN project results will have a direct impact on clinical practice, improving the appropriateness of antibiotic prescribing policy, the prevention of antibiotic-resistant infections and the heightener of patients' quality care.

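### Colonisation pressure is defined per centre, but infection risks are promised adjusted for ward colonisation pressure, so ward-level confounding can remain in three analyses

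*Protocol article*

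**What the plan says.** The case-control studies are numbered here as in the Statistical analysis section; the Abstract lists them in the other order.

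- **Definition (Statistical analysis).** "The colonisation pressure will be calculated for each center and defined as the average point of prevalence for antibiotic-resistant bacteria", averaged "for all days until acquisition or discharge". This is the only definition in the article.
- **Promised adjustment (Implications of the hypothesis).** The expected results include "risks for nosocomial infections due to target ARB after a cycle of antibiotic therapy adjusted by length of hospitalisation and ward colonisation pressure".
- **Setting (Presentation of the hypothesis).** There are three hospitals. "Overall, 6 medical and 6 surgical wards will be included".
- **Motivation (Background).** No earlier prospective multicentre cohort is said to have estimated the effect of antibiotics "after accounting for individual and group-level confounding variables, such as case-mix and colonisation pressure". No level is given for colonisation pressure.
- **Control for ward in the analyses (Statistical analysis).** Case-control study 1, antibiotics against none, takes controls "admitted in the same ward on the day of the corresponding case". Case-control study 2, on specific antibiotics, states a 1:4 ratio and no ward matching. The Cox model is described without a ward stratum or ward term.

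**The concern.** The unit of measurement and the unit of adjustment differ. Two patients in a medical and a surgical ward of the same hospital, followed over the same days, receive the same colonisation pressure even if carriage in the two wards is very different. The averaging window lets the value vary between patients by calendar time, but it carries no information about differences between wards at the same time.

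If wards of one hospital differ both in which antibiotics they use and in how readily resistant bacteria are acquired there, a drug used mainly in the high-carriage ward will look harmful without being so. Case-control study 2 is meant to compare specific antibiotics, so a distortion of this kind could change how drugs rank. The infection analysis is the one for which ward adjustment is explicitly promised.

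**Working it through.** **Step 1: set the sections side by side.** The plan gives no figure for this point, so there is none to reproduce.

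| Analysis | Ward control stated | Effect of a centre-level covariate |
|---|---|---|
| Infection risk | Ward pressure promised, not defined | Cannot separate wards of one hospital |
| Cox model, time to acquisition | None stated | Same |
| Case-control study 2 | None stated | Same |
| Case-control study 1 | Controls from the same ward | Ward controlled by design if matched sets are kept |

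**Step 2: hand illustration.** All inputs are assumed, because the documents give neither ward prevalence nor ward antibiotic use. Take two equal wards, A and B, of one centre. A drug with no effect is used in 60% of patients in A and 30% in B. The hazard is *h* in A and 1 in B.

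- Mean hazard in users: (0.6*h* + 0.3)/0.9
- Mean hazard in non-users: (0.4*h* + 0.7)/1.1
- *h* = 1: 0.9/0.9 = 1 and 1.1/1.1 = 1; ratio 1.00
- *h* = 2: 1.5/0.9 = 1.667 and 1.5/1.1 = 1.364; ratio 1.22
- *h* = 3: 2.1/0.9 = 2.333 and 1.9/1.1 = 1.727; ratio 1.35

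With the higher hazard in B instead, the mean hazards are (0.6 + 0.3*h*)/0.9 and (0.4 + 0.7*h*)/1.1:

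- *h* = 2: 1.333 and 1.636; ratio 0.81
- *h* = 3: 1.667 and 2.273; ratio 0.73

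A covariate with the same value in A and B leaves all of these unchanged.

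**Step 3: simulated illustration.** Assumed: three centres with four wards each; centre prevalence 5%, 15% and 10%; acquisition risk equal to half the ward prevalence (mean about 5%); average use of one drug class 30%; true odds ratio 1. Within each centre, ward prevalence and drug use vary together by the factors 1−s, 1−s/3, 1+s/3 and 1+s. Logistic regression was fitted to 8,565 × 40 = 342,600 simulated patients, so that bias and not chance is seen.

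| s | OR, centre pressure | OR, ward pressure | OR, ward as factor |
|---|---|---|---|
| 0 | 1.01 | 1.01 | 1.01 |
| 0.25 | 1.04 | 0.99 | 0.98 |
| 0.50 | 1.22 | 0.99 | 0.99 |
| 0.75 | 1.58 | 1.01 | 1.00 |

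With centre-level adjustment the bias grows with the variation between wards. Ward-level adjustment, or a ward factor, brings the estimate back to about 1.

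**The case against.** The strongest reply is that this is a wording mismatch in a condensed article and that nothing shows a biased result. Much of that is right, and it sets the limits of the point.

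- A reader might infer that ward adjustment was promised for the antibiotic effects on acquisition. It was not: the phrase belongs to nosocomial infection risk, a different outcome.
- A reader might infer that ward confounding stays in all antibiotic effects. Case-control study 1, which estimates the effect of antibiotics against none, draws controls from the same ward.
- A ward term is not ruled out in the Cox model or case-control study 2. Full covariate lists are commonly left to a longer document. Ward transfers and room sharing with a positive patient are recorded, and room sharing captures part of the local exposure.
- A reader might infer that MRSA and ESBL prevalence are pooled. The article uses antibiotic-resistant bacteria as a generic term and defines the assessable population by target organism, so pooling is only one reading.
- A reader might take the Background to name ward pressure as the confounder missed by earlier studies. It gives colonisation pressure as one example, beside case-mix, at an unspecified group level.
- The illustrated sizes rest on assumed inputs. The bias is nil without variation within a centre and changes sign if use and hazard run in opposite directions.

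What remains is that the article itself fixes the level, states it in two places, and the two do not agree. That is a conflict in the text, not a detail left out. Room sharing does not replace a ward measure, and a ward term that is merely possible is not a planned one.

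**Conclusion.** The point holds in limited form. As defined, colonisation pressure cannot provide the ward adjustment that the article promises for infection risk. The same definition leaves room for ward-level confounding in the Cox model and case-control study 2. It does not show that confounding is present, and it does not reach case-control study 1 as long as the matching is respected in the analysis.

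The size is unknown. Under the hand illustration a null drug shows a ratio of 1.00 to 1.35 when use and hazard are aligned and falls below 1 when they are opposed. The simulated odds ratio runs from 1.01 to 1.58 over the assumed range of variation between wards. These figures show what is possible and are not forecasts for this study. The conflict should be resolved before analysis, at low cost.

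**What to change.** In the Statistical analysis section, define colonisation pressure per ward and period (for example weekly), separately for MRSA and ESBL, from the screening results already collected. Enter it in the infection analysis, the Cox model and case-control study 2.

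Alternatively, stratify the Cox model by ward and match or condition on ward in case-control study 2. This removes stable differences between wards, but not changes over time within a ward. It also does not by itself supply the ward pressure promised for infection risk, so that sentence would then have to state the adjustment actually made.

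In either case, align the definition with the sentence under Implications of the hypothesis, and state that case-control study 1 will be analysed with its matched sets kept.

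The cost is analysis wording and programming; no new data collection is apparent. Ward-level prevalences are noisier than centre averages. Swabs are intermittent, and patients positive at antibiotic start have no follow-up cultures, so the plan must state how carrier status between swabs is assumed. Clustering standard errors on only 12 wards would be unreliable without a small-sample correction and is not needed for this fix.

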### Sample size

Since the rate of acquisition of ESBL-producing gram-negative bacteria in patients receiving antibiotic therapy has not been established in prospective cohort studies, prevalence proportion was derived from retrospective case-control studies and defined as 5%. Sample size calculation for the rate of new acquisition of MRSA has been derived by a previous study where the acquisition rate, after starting antibiotic therapy, was 3% [4]. To be able to analyse 257 patients newly colonised by MRSA and 443 by ESBL-producing gram-negative, 8565 patients starting antibiotic therapy need to be enrolled. According to the number of hospital admission/year and percentage of patients starting antibiotic in each ward, the clinical centers are required to provide the following numbers of patients with new colonisation by MRSA/ESBL *Enterobacteriaceae*: 48/95, 121/201, and 88/147 for UCSC, IDMB, CCS, respectively.

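### One minus Kaplan-Meier overstates the proportion who acquire resistant bacteria: slightly because deaths are censored, substantially only if the curve is read as in-hospital acquisition with every discharge censored

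*Protocol article*

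**What the plan says.** For time from inclusion to acquisition, the Statistical analysis section of the protocol article names "Kaplan-Meier curves and Cox proportional hazard regression modeling in which the number of days until acquisition will be the dependent variable". It names no competing-event method. The analysis set is "all treated patients from whom baseline screening and at least one follow-up screening will be available", restricted to patients negative at baseline.

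The section Testing the hypothesis sets the follow-up: "Patients will be followed during the hospitalisation and afterwards for a total of 30-day from the inclusion in the study". Outpatient screening is planned after "discharge from the hospital, if possible". The Abstract also plans a swab at discharge itself.

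Under Outcomes, "The primary outcome will be the rate of acquisition of target antibiotic bacteria by 1,000 antibiotic-days in hospitalised patients". No cumulative proportion from a Kaplan-Meier curve is listed as an outcome.

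**The concern.** A patient who dies can no longer acquire MRSA or ESBL-producing bacteria. Kaplan-Meier removes that patient from the risk set as if they would later have acquired at the same rate as those still observed. The curve then estimates risk in a setting where nobody dies, which is higher than the proportion who actually acquire.

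Discharge is less clear-cut because the article supports two readings of the target. The primary outcome is worded for hospitalised patients, and the Background speaks of nosocomial carriage. On that reading discharge ends the period at risk and competes with acquisition, as death does. Follow-up, however, continues to day 30 after discharge. On that reading a discharged patient can still acquire and be detected, and one who is not swabbed again is incompletely observed.

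At stake is any absolute acquisition risk read from the curve. If antibiotic groups differ in stay or mortality, the curve departs from the actual proportion by a different amount in each. That matters for selective screening, a possible use of the results named under Implications of the hypothesis.

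**Working it through.** **Inputs from the article.** For MRSA, "the acquisition rate, after starting antibiotic therapy, was 3"%. For ESBL, "prevalence proportion was derived from retrospective case-control studies and defined as 5"%. The targets are "257 patients newly colonised by MRSA and 443 by ESBL-producing gram-negative", from 8565 patients.

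**The plan's own figure.** 257 / 0.03 = 8567, against 8565 stated, and 8565 × 0.03 = 257. The MRSA figure therefore reproduces as a simple proportion of enrolled patients. (The ESBL target is 443 / 8565 = 5.17%; at 5% it would be 428. This has no bearing here.) I use 3% and 5% as the true 30-day proportions. The article does not state their time horizon, so 30 days is an assumption.

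**Assumed, because the article does not give them:** constant hazards, mortality, exit times, the share swabbed after discharge, and the change in hazard after discharge.

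**Formulas.** Let λ be the acquisition hazard and μ the hazard of the other exit.
- True proportion by day 30: λ/(λ+μ) × [1 − exp(−30(λ+μ))]. Solve for λ so that this equals 0.03 or 0.05.
- One minus Kaplan-Meier, with the other exit censored: 1 − exp(−30λ).

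**(a) Death is the only competing event.** μ = −ln(1 − d)/30 for 30-day mortality d.

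| d | true 3% reads | true 5% reads | ratio |
|---|---|---|---|
| 2% | 3.03% | 5.05% | 1.01 |
| 5% | 3.08% | 5.13% | 1.03 |
| 10% | 3.16% | 5.27% | 1.05 |
| 20% | 3.35% | 5.57% | 1.12 |

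Example at d = 20%: μ = 0.00744, λ = 0.00113, and 1 − exp(−30λ) = 3.35%.

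**(b) In-hospital target, every discharge censored.** μ = 1/(mean time to exit).

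| mean exit | true 3% reads (ratio) | true 5% reads (ratio) |
|---|---|---|
| 10 days | 9.3% (3.09) | 15.2% (3.05) |
| 15 days | 6.9% (2.29) | 11.4% (2.27) |
| 20 days | 5.8% (1.92) | 9.5% (1.91) |
| 30 days | 4.7% (1.58) | 7.9% (1.57) |

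Example at 10 days: μ = 0.1, λ = 0.00551, and 1 − exp(−30λ) = 15.2%. The ratio hardly changes between 3% and 5%, so a low acquisition rate does not make the relative bias small.

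**(c) Target is acquisition by day 30 wherever the patient is.** Here the hazard is λ in hospital and r × λ after discharge, and a share f is still swabbed after discharge. The true proportion counts everyone. The Kaplan-Meier hazard averages over inpatients and swabbed outpatients only. The true proportion is set to 3% and the median stay to 7 to 15 days.

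| hazard after discharge | all swabbed | half swabbed | none swabbed |
|---|---|---|---|
| unchanged | 1.0 | 1.0 | 1.0 |
| halved | 1.0 | about 1.09 | 1.3 to 1.5 |
| quartered | 1.0 | 1.15 to 1.17 | 1.5 to 2.0 |

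**(d) Comparing groups.** Give two groups the same λ = 0.0025 per day and mean exits of 10 and 20 days. One minus Kaplan-Meier is 1 − exp(−0.075) = 7.2% in both, while acquisition before exit is 2.3% and 3.8%. The curve does not create a difference from exit rates. It departs from the actual in-hospital proportion by different amounts.

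**The case against.** The strongest reply is that this is a condensed article, it states no censoring rule, and such rules commonly sit in a full protocol or analysis plan. That stands as far as missing detail goes. The estimator, however, is a stated choice, and an ordinary Kaplan-Meier curve censors deaths. Treating death as a competing event would be a different estimator, and none is named.

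The second reply is that discharge is not a competing event when follow-up runs to day 30, so the large ratios in (b) do not apply to that target. This is correct. A reader might infer that the plan overstates 30-day acquisition about threefold. The documents do not support that, because (b) counts acquisition after discharge as zero. For the 30-day target the ratio is 1.0 if the hazard is unchanged after discharge or all are swabbed, and reaches 2.0 only at the extreme of the ranges tried. Counting unswabbed discharge as competing for that target would treat those patients as never acquiring, and so understate the risk.

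The third reply is that no listed outcome is a Kaplan-Meier proportion. That also stands. A reader might infer that the primary result or the Cox comparisons are invalid. The primary rate is events over antibiotic-days and does not come from this curve. A Cox model that censors deaths still estimates a cause-specific hazard ratio.

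**Conclusion.** The point holds in a limited form. Kaplan-Meier is the wrong estimator for an absolute acquisition risk when death competes, but death alone moves it little: a relative excess of about 1% to 12% for assumed 30-day mortality of 2% to 20%. The bias is large, about 3.1 to 1.6 times for assumed mean exit times of 10 to 30 days, only if the curve is read as in-hospital acquisition and all discharges are censored. For acquisition by day 30 in any setting, the excess is 0% to 17% with half or more swabbed after discharge and 0% to 100% with none swabbed, over the hazard reductions tried.

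All these sizes rest on constant hazards and on exit, mortality and swabbing figures that the article does not contain. The mortality that matters is that of the analysis set, which requires a follow-up swab and so leaves out patients who die before one is taken. The primary rate is unaffected, and the Cox model can stay. This is a worthwhile, inexpensive improvement to a supporting analysis.

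**What to change.** - State whether absolute risk means in-hospital acquisition or acquisition by day 30 in any setting.
- For any absolute risk, replace one minus Kaplan-Meier by the Aalen-Johansen cumulative incidence, with death as a competing event.
- Count discharge as a competing event only for an explicitly in-hospital target.
- For the 30-day target, censor discharged patients at their last swab if none follows, and report the share swabbed after discharge by antibiotic class. This does not remove bias if risk changes after discharge, but it shows how much rests on that assumption.
- Keep the Cox model and label it cause-specific.

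The cost is a few sentences and standard code. The analysis uses dates of death and discharge and the swabs already planned. The reported risks become slightly lower where only death competes, and clearly lower if an in-hospital target is chosen and many patients leave early.
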